## 1 Abstract

**Background:** Older adult caregivers of people experiencing psychosis can experience many physical and mental health difficulties. There is currently little to no provision in healthcare services to meet these needs of caregivers. Due to the demands of caregiving, any intervention would need to be time-limited, and able to fit in around caring activities.

**Methods/Design:** This study proposes a pilot randomised controlled trial of a self-directed writing therapy called Positive Written Disclosure, compared to a writing control task and a non-writing control group. The study will recruit older adults (aged 50 or over) who currently provide care for someone experiencing psychosis. Positive Written Disclosure will require participants to take 20 minutes out of their day for three consecutive days to write about a positive memory. The writing control task will involve participants writing about a neutral image in a factual and objective way. The non-writing control task will receive no intervention.

**Discussion:** As this is a pilot randomised controlled trial, the results of this study will help to determine whether a definitive trial is warranted, and if so provide the indices to estimate the relevant parameters required for power calculations.

## 2 Keywords

Written emotional disclosure, carers, psychosis, older adults, pilot, randomised controlled trial, positive written disclosure.

## 3 List of abbreviations

WED = Written emotional disclosure  
 PWD= Positive written disclosure  
 WC= writing control  
 NWC= non-writing control  
 RCT= randomised controlled trial  
 PIS= participant information sheet  
 TBC= to be confirmed  
 CRC= clinical research coordinator  
 GP= general practitioner

## 4 Background

Of the 6.4 million caregivers in Britain, one in four cares for someone with a mental illness (Buckner & Yeandle, 2011). In response to a survey on mental health caregivers, the majority (57%) were found to be over 60, with 32% 60-69, 20% 70-79 and 5% over 80 (Pinfold & Corry, 2003). The caregiver role is vital both for the

person cared for and for society as a whole. The costs of caregiving for individuals with schizophrenia alone are estimated at £11.8 billion per year (Knapp, McCrone, Parsonage & Trachtenberg, 2012). If informal caregivers stopped providing this care many more vulnerable people would need the support of NHS services at an estimated total cost of £36,000 per annum per person with schizophrenia (Knapp, McCrone, Parsonage & Trachtenberg, 2012).

Caregiving is physically, mentally and emotionally demanding and has been identified as a risk factor for health problems; up to 40% of caregivers experience psychological distress and depression, and high levels of care provision is associated with a 23% increase in risk of stroke (Haley, Roth, Howard & Sarrod, 2010; Pinquart & Sorenson, 2003). These adverse health effects result from the physical effort required in caregiving, and/or dealing with the behavioural problems of the care recipients (Pinquart & Sorenson, 2003), as well as 'indirect' effects such as less time, energy and finances available for normal daily living. Caregivers are often mentally and physically exhausted by their caregiving role and may find it difficult to engage in leisure/social activities or paid employment (Oyebode, 2003). Approximately one in five caregivers give up work to care and more than half fall into debt as a result of their caregiver duties (Carers UK, 2007; Carers UK, 2008). Indeed, level of caregiver distress has been found to correlate with the number of hours and number of caregiving tasks per week (Hirst, 2005; Martire, Manela, Shuttleworth & Livingstone, 1997).

Surprisingly, very few studies have explored ways to alleviate stress and improve caregivers' psychological and physical wellbeing (Martire, Manela, Shuttleworth & Livingstone, 1997). Psychosocial therapies such as community support groups and cognitive behavioural skills training show some effect on the wellbeing of caregivers of people with physical illnesses, such as cancer, heart disease or arthritis (Martire, Lustig, Schulz, Miller & Helgeson, 2004). Psycho-educational therapies are considered most effective in helping caregivers of individuals with dementia (Alzheimer's disease and others) (Sorenson, Duberstein, Gill & Pinquart, 2006). These therapies typically tend to improve knowledge of the condition, but have only a small effect on cares' psychological wellbeing and depression (Sorenson, Duberstein, Gill & Pinquart, 2006). NICE (2002) recommends that family therapies should be offered to all families of people with schizophrenia for at least 6 months. However, these therapies are difficult to implement, and an audit in East Sussex revealed that family therapies were only deemed appropriate in 42% cases (Beeton, Meddings & Gibbins, 2008). In addition, attending family therapy for a prolonged period is often impractical for those families most in need. Therefore there remains an urgent need for an easily accessible and effective therapy for caregivers of patients with severe mental illness.

A psychological therapy which has received much empirical attention in both clinical and non-clinical populations is written disclosure (see Frattaroli, 2006 for a review). The therapy typically involves writing about a stressful or traumatic experience for 20 minutes a day over three consecutive days and is found to have significant effects on a range of measures of physical and psychological wellbeing. However, very limited benefits have been found in caregivers (Barton & Jackson, 2009; Mackenzie, Wiprzycka, Hasher, Goldstein, & Mackenzie, 2007; Smith et al., 2015). One small study found that caregivers who wrote about positive rather than

traumatic experiences reported greater improvements in psychological wellbeing (Mackenzie, Wipryzcka, Hasher & Goldstein, 2008). Positive written disclosure (PWD) follows an identical format, but participants are asked to write about positive rather than traumatic experiences.

We know from previous research, that positive written disclosure (PWD) in healthy populations reduces health complaints and health care utilisation, and improves mood and life satisfaction (Burton & King, 2004; Burton & King, 2008; Wing, Schutte & Byrne, 2006). Most recently in caregivers, a larger more rigorous three-armed study on 150 informal caregivers trialling positive, traumatic and control writing tasks showed that for some caregivers, writing about positive experiences led to decreased anxiety and depression 2-weeks, 2-months and 6-months later (Ashley, O'Connor & Jones, 2011). Previous studies have reported a strong beneficial effect of positive writing on wellbeing (Burton & King, 2004; Burton & King, 2008; Wing, Schutte & Byrne, 2006). In contrast, no improvement was found for those caregivers who undertook the traumatic writing. Although these findings are promising, this study included a wide range of caregivers, including caregivers of those of any age with physical or mental illness, addiction or disability. These findings cannot be generalised or extrapolated to caregivers of people with psychosis, as these caregivers are generally older and experience greater emotional strain, increased stigma and poorer satisfaction with support given issues around confidentiality and information-sharing (Lindon, 2007).

#### 4.1 *Research question*

This is a pilot study that aims to answer a number of feasibility questions that will determine whether a definitive trial is justified, and if so the design of this trial. Specifically this pilot trial aims to answer the following questions:

- a) Are carers of people with psychosis willing to be recruited and randomised?
- b) Are there retention issues? If yes, at what stages did these occur? What were the reasons?
- c) Are follow-up data complete i.e. no more than 33% attrition?
- d) Can the positive written disclosure (PWD) be delivered with sufficient fidelity?
- e) Is there sufficient evidence for scaling up to a definitive randomised controlled trial?
- f) What sample size is needed to power a full scale randomised controlled trial?
- g) Are there any safety issues or adverse events related to the completion of writing tasks?
- h) What did the carers think of the intervention and study design?

The research question for the definitive trial will be: Does positive written disclosure (PWD) improve both the psychological and physical wellbeing of older adult carers of

people with psychosis compared to a writing (WC) and non-writing control (NWC) condition?

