### 6.5 Assessment process

| Assessment                   | Carried out by | What the assessment is for                                  | How is the assessment carried out            | At what stage is the assessment carried out |
|------------------------------|----------------|-------------------------------------------------------------|----------------------------------------------|---------------------------------------------|
| Baseline Assessment          | RF or RA       | Measure outcomes before randomisation                       | In person
Online or paper based           | After consent                               |
| 1 month assessment           | P              | Measure outcomes post intervention                          | Via post
Online or paper based            | 4 weeks post randomisation                  |
| 3 month follow up assessment | P              | Measure outcomes at short term follow up time point         | Via post
Online or paper based            | 12 weeks post randomisation                 |
| 6 month follow up assessment | P              | Measure outcomes at long term follow up time point          | Via post
Online or paper based            | 24 weeks post randomisation                 |
| Exit interview               | RF or RA       | Generate qualitative data on participants experience of PWD | In person or via telephone
Audio recorded |                                             |

RF= Research Fellow

RA= Research Assistant  
P= participant

The assessment will take place in either the participants own home or in a convenient NHS building (e.g. GP surgery or mental health building). Where assessments are carried out in the participant's home, the lone working policy will be followed (see section 9 – ethical considerations). The assessments at the 1, 3 and 6 month time points will not require any direct contact with the research team. The participants will be sent the assessment pack in the post with a covering letter. They will be asked to complete the questionnaires and return them in a pre-post envelope. Participants will also have the option to complete all assessments online (except for the exit interview).

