#### 6.7 *Procedure*

The study procedure is outlined in a CONSORT diagram (see below).

Once participants have been randomised to one of the three conditions: (1) PWD, (2) WC, or (3) NWC; they will be informed of the condition they have been allocated to and the relevant next steps. For participants in the NWC group they will be given an empty writing pack and will be asked to continue with their usual daily activities, and wait to receive the one month assessment pack. For those in the PWD or WC groups, they will receive their writing task and the relevant paperwork for this (see section 6.8 for details of the writing tasks).

There will be no further contact between the research team and the participants until the one month assessment – however participants will have the contact information of the research team in the event they need to make contact. At the one month assessment point, participants will be sent an assessment pack. Participants will be asked to complete some questionnaires and return them in a pre-post envelope within a week of receiving them. If participants were allocated to one of the writing conditions (PWD or WC) then we will also ask them to return their writing tasks. The writing tasks will be read by either CJ or MH to check for any signs of distress or risk. A copy of the writing tasks can be returned to the participants at a later date upon their request.

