### 7.2 Research Variables Form (RVF)

The table below details all of the assessments that will be carried out over the course of the study, and at what time point they will be carried out.

| Type of data           | Variable name         | Outcomes/units | Source/Any Instructions |
|------------------------|-----------------------|----------------|-------------------------|
| Eligibility assessment | Eligibility Questions | 6 items        | None                    |
| Baseline assessment    | Demographics          | 25 items       | None                    |
|                        | DASS 21               | 21 items       | Lovibond, 1983          |
|                        | PANAS                 | 20 items       | Watson et al., 1988     |
|                        | GSE                   | 10 items       | Schwarzer &             |

|                    |                     |          |                             |
|--------------------|---------------------|----------|-----------------------------|
|                    |                     |          | Jerusalem, 1995             |
|                    | CWSv2               | 32 items | Quirk et al., 2009          |
|                    | TAS 20              | 20 items | Bagby et al., 1994          |
|                    | EQ-5D               | 6 items  | Taylor et al., 1992         |
|                    | LTS                 | 6 items  | Stevens et al., 2010        |
| 1 month assessment | Demographic changes | 6 items  | None                        |
|                    | DASS 21             | 21 items | Lovibond, 1983              |
|                    | PANAS               | 20 items | Watson et al., 1988         |
|                    | GSE                 | 10 items | Schwarzer & Jerusalem, 1995 |
|                    | CWSv2               | 32 items | Quirk et al., 2009          |
|                    | EQ-5D               | 6 items  | Taylor et al., 1992         |
|                    | LTS                 | 6 items  | Stevens et al., 2010        |
| 3 month assessment | Demographic changes | 6 items  | None                        |
|                    | DASS 21             | 21 items | Lovibond, 1983              |
|                    | PANAS               | 20 items | Watson et al., 1988         |
|                    | GSE                 | 10 items | Schwarzer & Jerusalem, 1995 |
|                    | CWSv2               | 32 items | Quirk et al., 2009          |

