## **10 Discussion of practical and operational issues**

Adverse events: The Good Clinical Practice guidelines will be followed in the event of any adverse events during the study. The procedure that will be followed is outlined here:

1. If any adverse event occurs this will be taken firstly to the trial manager (CH)
2. The adverse event will then be rated on a 5 point scale for severity and a separate 5 point scale for relevance to the study
3. If the event is deemed to be severe, then this will be taken to the Chief Investigator (CJ) and the wider research team (MH, HS, DO, VP)

4. If there is a cause for concern (i.e. an adverse event was rated as both severe and relevant to the study) this would then be taken to the Trial Steering Committee and the sponsor (the University of Sussex)
5. Both parties will then make a decision as to whether the adverse event needs further investigation, and whether the study needs to be stopped
6. The outcome of any investigation will then determine the future of the study (e.g. whether the study is able to resume again, and if so, when it can resume)

Any severe and relevant adverse events that occur during the research will also be reported to the ethics committee, in line with NHS ethics protocol. Additionally, the participants GP will be informed about the adverse event. Emergency services will also be contacted where needed.

Both the trial manager (CH) and the principal investigator will take joint responsibility for informing both the Trial Steering Committee and the sponsor of any adverse events. Both parties will be informed via email – all emails related to this will be marked as urgent.

Managing risk: In the event there are risk-related issues brought to the attention of the research team (i.e. when a clinician makes a study referral), the study protocol will be adapted to manage these in a safe way. Where the risk is too high and involvement in the research study may put the participant at any further risk, they will not be recruited to participate.

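### No listed assessment asks about adverse events, and the passive routes differ by arm, so adverse-event counts for the writing arms against the non-writing control are confounded by ascertainment

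*Protocol*

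**What the plan says.** Question (g) of section 4.1 asks: "Are there any safety issues or adverse events related to the completion of writing tasks". It is one of the feasibility questions that decide whether a definitive trial is justified.

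Section 7.2 introduces its table with: "The table below details all of the assessments that will be carried out over the course of the study". After baseline, each time point holds a six-item demographic-changes form and six questionnaires (DASS-21, PANAS, GSE, CWSv2, EQ-5D, LTS). No adverse-event item is listed.

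Contact with the team is minimal. Section 6.7: "There will be no further contact between the research team and the participants until the one month assessment". Section 6.5: "The assessments at the 1, 3 and 6 month time points will not require any direct contact with the research team". Participants hold the team's contact details, and section 6.7 allows a telephone assessment as a fallback.

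At one month, section 6.7 adds a step for two arms only: "If participants were allocated to one of the writing conditions (PWD or WC) then we will also ask them to return their writing tasks". Two named team members read what comes back "to check for any signs of distress or risk".

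Section 10 starts from an event that is already known: "If any adverse event occurs this will be taken firstly to the trial manager". It then sets out rating scales for severity and for relevance to the study, and an escalation path.

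**The concern.** A pilot that asks about the safety of writing needs a way to find events, and the same way in every arm. As written, an event comes to notice if a participant volunteers it, if a returned workbook shows distress, or if it surfaces in an exit interview. The last two routes do not exist in NWC. Section 6.8.3 gives NWC the job of separating the act of writing from its content, so NWC is the natural reference for harm from writing. A higher recorded count in PWD or WC could reflect closer looking and nothing else.

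The opposite error also matters. A writer who becomes distressed, stops and returns nothing may leave no trace, so a low count in the writing arms would not be reassuring either. An SAP cannot repair this later, because it cannot recover events that nobody asked about.

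**Working it through.** The protocol states no figure on this point, so there is none to reproduce. The check sets the routes side by side.

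| Route (section) | PWD | WC | NWC | Limit |
|---|---|---|---|---|
| Adverse-event question at 1, 3, 6 months (7.2) | not listed | not listed | not listed | – |
| Participant contacts the team (6.7) | yes | yes | yes | self-initiated |
| Fallback phone or face-to-face assessment (6.7, 7.8) | yes | yes | yes | exceptional; no event question listed |
| Workbook read for distress (6.7) | yes | yes | no | only if returned |
| Exit interview (6.7, 7.1) | yes | yes | no | after all quantitative data |
| Exit interview (11) | yes | no | no | week 27 |
| Anonymous feedback forms (6.3) | not stated | not stated | not stated | absent from the 7.2 table |
| DASS-21 and PANAS negative affect (6.9, 7.2, 7.8) | yes | yes | yes | not named as safety measures |

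**How many writers may return no workbook.** Inputs: 60 recruited and 12 completers per arm (7.3), 1:1:1 allocation (6.6), 33% attrition limit (4.1).
- Per arm: 60 / 3 = 20.
- A completer has baseline and 1 month data, and workbooks are requested at 1 month. The completer target is met even if 20 − 12 = 8 of 20 (40%) in an arm send back no 1 month pack.
- At the 33% limit: 20 × 0.33 = 6.6 lost, leaving 13.4 per arm.

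**How large an artefact could be.** The documents give no event rate and no detection probability, so these values are assumptions. Expected recorded events = n × p × d, with n = 20, the same true rate p in each arm, and detection d differing by arm.

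| p | d, writing arm | d, NWC | Recorded, writing arm | Recorded, NWC | Ratio |
|---|---|---|---|---|---|
| 0.10 | 0.8 | 0.2 | 1.6 | 0.4 | 4 |
| 0.10 | 0.6 | 0.3 | 1.2 | 0.6 | 2 |
| 0.20 | 0.8 | 0.2 | 3.2 | 0.8 | 4 |
| 0.20 | 0.6 | 0.3 | 2.4 | 1.2 | 2 |

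The ratio equals the ratio of the two detection probabilities and does not depend on p. It comes from ascertainment alone.

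**Two inconsistencies met on the way.**
- Sections 6.7 and 7.1 give exit interviews to both writing arms; section 11 gives them to PWD only. The PWD-only version would also make PWD and WC unequal.
- Steps 3 and 4 of section 10 pass an event to the Trial Steering Committee and sponsor when it is rated severe and also study-related. A later paragraph of the same section says that two roles "will take joint responsibility for informing both the Trial Steering Committee and the sponsor of any adverse events".

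**The case against.** The best case for the plan is that (g) concerns events related to the writing tasks and promises no comparison between arms. NWC has no task, and section 10 rates each event for its relevance to the study. This is right as far as it goes, but a relevance rating can be given only to an event that has been found.

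A reader might infer that (g) cannot be answered by comparing arms at all. The documents do not support that. PWD and WC workbooks are requested and read in the same way, so those arms can be compared among participants who return them. DASS-21 and PANAS negative affect are collected in all three arms with the same pack (7.8).

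A reader might also infer that NWC is bound to look free of events because nobody looks there. That too goes beyond the text. NWC participants can contact the team, may have a fallback phone assessment, and complete the same distress scales. Under-recording is likely; an empty column is not certain. Question (b) of section 4.1 also asks why participants leave, so some drop-outs may give a reason.

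The booklets are in appendices that are not shown (section 15), the six demographic-changes items are unspecified, and the 7.2 table omits the feedback forms named in section 6.3. Absence from the table is therefore good evidence, not proof.

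Finally, the arms are small. With 20 per arm and no events in one, five are needed in the other for a two-sided Fisher p below 0.05 (p = 0.047). Asking everyone makes counts fair but leaves a comparison of arms weak. For the same reason, an upper confidence limit for zero events would not measure this problem: it describes the arm size and would be unchanged by the fix.

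On section 10, the later sentence may be meant only to say who sends the notifications and how. Its literal wording still covers every event.

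**Conclusion.** The point holds in a limited form. The protocol lists no systematic question about adverse events in any arm, and its passive routes favour the writing arms. Under-recording is likely, chiefly in NWC and among writers who drop out. Raw event counts for PWD or WC against NWC are confounded by ascertainment, and few or no recorded events would say little about (g).

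The two- to four-fold gap illustrates the mechanism under assumed detection rates; it is not an estimate. The conclusion rests on the 7.2 list being complete, as that section says it is. If the unseen booklets already contain such an item, the point reduces to listing it there. This is a cheap and worthwhile improvement to data collection, not a defect that undermines the pilot. The section 10 and exit-interview inconsistencies are separate and minor.

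**What to change.** - Add one identical, arm-neutral adverse-event item to the 1, 3 and 6 month packs in all arms, and ask it in the fallback phone assessments. It could cover a new or worse health problem, distress, or hospital or crisis contact since the last questionnaire. It should not mention writing, so that answers do not reveal allocation. List it in section 7.2.
- Tabulate the answers by arm and time point, with the number who answered as denominator, and report workbook findings separately with the number returned.
- Tabulate worsening on DASS-21 by arm as a supporting safety measure. The data are already collected.
- Reconcile sections 6.7 and 7.1 with section 11 on who is offered an exit interview.
- Reconcile the two statements in section 10 on which events go to the Trial Steering Committee and sponsor. Which rule applies is for the sponsor to decide.

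The cost is one question on a form that every arm already receives, and one or two tables. The small downside is that more events will be recorded and will need rating and processing.
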